### Criteria for discontinuing or modifying allocated interventions {11b}

Participants will be free to withdraw from the study at any time. In addition, subjects may be withdrawn at the discretion of the investigator if the subject is non-compliant with the protocol. Further detailed information will be explained in the study results.

### Strategies to improve adherence to interventions {11c}

Participants will be provided with selenium and placebo tablets during weeks 1 and 6. At baseline, instructions on how to use their supplements will be provided. They will be asked to return the remaining tablets at week six and end of the trial. Moreover, any side effects that they experience will be recorded. Adherence to intervention refers to how participants’ behavior aligns with their assigned intervention, which will be evaluated by phone call and counting the returned tablets at the end of the trial. Compliance will be calculated using the following formula:$$\mathrm{Compliance rate}=\left(\mathrm{tablets taken}/\mathrm{tablets prescribed}\right)\times 100$$

### Relevant concomitant care permitted or prohibited during the trial {11d}

The routine care and treatment provided by a neurologist, will remain unchanged during the study. Participants will only receive selenium supplements or a placebo in addition to standard treatments.

### Provisions for post-trial care {30}

Selenium or placebo supplements will only be administered for 12 weeks. Regular care and treatments will also continue after the trial concludes.

### Outcomes {12}

The primary outcome of the present study is to investigate the effect of selenium on oxidative stress and clinical symptoms in migraine patients. Secondary outcomes include mental health status and participants’ quality of life.

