### Additional consent provisions for collection and use of participant data and biological specimens {26b}

Participants will be requested to provide consent for the review of their medical records and blood sample collection to assess oxidative stress biomarkers, including nitric oxide (NO), total antioxidant capacity (TAC), total oxidant status (TOS), and malondialdehyde (MDA). Participants will also provide consent for using their data in future publications, which is not obligatory.

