### Sample size {14}

The sample size was calculated based on means and standard deviations for the primary variable, which is MDA levels, reported in the study of Razavi et al. [19], considering a type I error of 5% (α = 0.05) and type II error of 20% (β = 0.20, power = 80%). Sample size was calculated using the following formula [20]:$$n=\frac{2{(\mathrm{a }+\mathrm{ b})}^{2} {\upsigma }^{2}}{{(\upmu 1 -\upmu 2)}^{2} }=33$$

*n* = the sample size in each group.

μ1 = the mean for malondialdehyde in the intervention group: -0.13 μmol/L based on the study of Razavi et al. [19]).

μ2 = the mean for malondialdehyde in the control group: 1.4 μmol/L based on the study of Razavi et al. [19]).

σ = the variance (SD) for mean concentrations of malondialdehyde: 4.00 (the average SDs reported for malondialdehyde in the control and intervention groups of Razavi et al.’s study [19]).

a = the conventional multiplier for alpha = 0.05 that was 1.96.

b = the conventional multiplier for power = 0.80 that was 0.842.

Based on the formula, we will need a sample size of 33 for each group. Considering a drop-out rate of 10%, we plan to recruit 36 migraine patients in each group.

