#### Migraine symptoms assessment

An expert neurologist will assess migraine characteristics, including severity, frequency, and duration of migraine attacks. Headache severity will be assessed using a visual analogue scale (VAS) questionnaire on a 0–10 scale with 0 representing "no pain" and 10 "the worst imaginable pain”. The Persian version of this questionnaire, validated by previous investigators, will be used [21]. The patients will note the feeling that represents their perception of pain. The frequency and duration of migraine headaches will be evaluated as the number of attacks per month and the mean duration of attack in each day, respectively.

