## Statistical methods

### Statistical methods for primary and secondary outcomes {20a}

To examine normal distribution of variables, the Kolmogorov–Smirnov test will be used. To normalize the non-normally distributed variables, we will conduct a log transformation. The intention-to-treat (ITT) approach will be used to estimate missing values on outcome variables. Independent sample t-test will be used to detect differences in quantitative variables between intervention and control groups. For the assessment of qualitative variables between the two groups, the chi-square test will be performed. The paired-sample t-test will also be used to examine within-group differences. One-way analysis of covariance (ANCOVA) will be performed to detect the effect of selenium supplementation on outcome variables. In this analysis, potential confounders will be taken into account. All statistical analyses will be conducted using the SPSS software version 21 (SPSS, Inc. Chicago, IL, USA). P-values less than 0.05 will be considered statistically significant.

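### The Outcomes section makes two multi-variable domains primary, the Sample size section names MDA alone, and no rule controls error across the variables at a flat 0.05

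*Protocol article*

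**What the plan says.** All references are to the protocol article.

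- **Outcomes {12}:** "The primary outcome of the present study is to investigate the effect of selenium on oxidative stress and clinical symptoms in migraine patients". No variable, metric or time point is attached. Mental health and quality of life are secondary.
- **Sample size {14}:** "The sample size was calculated based on means and standard deviations for the primary variable, which is MDA levels". It uses a type I error of 5% with multiplier 1.96, so two-sided, and 80% power.
- **Measures of the two primary domains:** the biomarker consent section {26b} and the specimen section {33} list NO, TAC, TOS and MDA. Migraine symptoms assessment describes migraine characteristics "including severity, frequency, and duration of migraine attacks".
- **Statistical methods {20a}:** "P-values less than 0.05 will be considered statistically significant". It lists an independent-samples t-test, a paired t-test ("The paired-sample t-test will also be used to examine within-group differences") and ANCOVA. ANCOVA is the method tied to the effect of selenium.
- **Additional analyses {20b}:** ANCOVA is to be adjusted for whatever differs significantly between the arms.

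No section gives a multiplicity adjustment, a testing order, a rule that all primary variables must succeed, or a statement of which variable decides the trial.

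**The concern.** A reader of Outcomes {12} sees two domains, each with several measures. A reader of Sample size {14} sees one laboratory variable. Both are current text, and the second calls MDA the primary variable outright, so it cannot be read as merely a convenient variable for sizing.

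The choice decides what a positive trial means. Suppose MDA shows nothing but one headache measure reaches P < 0.05. Under one section the trial has a positive primary result; under the other it has failed on its primary and has a secondary signal. With the choice left open until results are known, the 5% type I error used to size the trial is not guaranteed. An analysis plan that is not shown could add detail, but it could not make both statements true.

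**Working it through.** **1. The plan's own figure.** The stated result is 33 per group for MDA, from n = 2(a + b)²σ²/(μ1 − μ2)², with a = 1.96, b = 0.842 and a difference of 1.4 − (−0.13) = 1.53.

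- If 4.00 is the variance: 2 × 2.802² × 4 / 1.53² = 26.8, so 27 per group.
- If 4.00 is the SD: 2 × 2.802² × 16 / 1.53² = 107.3, so 108 per group.

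Neither gives 33, which would need a variance of about 4.92. The article labels 4.00 as both variance and SD. That is a separate defect and this point does not depend on it, but it is why the power figures in step 4 come in pairs.

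**2. Counting the variables.** Oxidative stress: NO, MDA, TAC, TOS (4). Clinical symptoms: severity, frequency, duration (3). Total 7.

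**3. Chance of at least one false positive.** This assumes no true effect, two-sided 0.05 for each variable, and any one variable counting as success.

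- One variable (MDA): 5%.
- Seven independent tests: 1 − 0.95⁷ = 0.302.
- Seven correlated tests: the document gives no correlations, so a common correlation is assumed and seven normal test statistics are simulated (400,000 draws).

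| Assumed common correlation | Chance of at least one P < 0.05 |
|---|---|
| 0 (exact) | 30% |
| 0.3 | 27% |
| 0.5 | 23% |
| 0.7 | 18% |
| 0.9 | 11% |

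The result is about six times the design level under independence and about twice at correlation 0.9. Even if each domain were reduced to one independent test, it would be 1 − 0.95² = 9.75%.

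**4. Power if all seven stay primary.** Holm's first step is 0.05/7 = 0.00714, with two-sided critical value 2.690. Power for the stated MDA difference at 33 per group is Φ(1.53 / (σ√(2/33)) − 2.690), where √(2/33) = 0.2462.

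- Variance 4 (σ = 2): Φ(3.107 − 2.690) = Φ(0.417) = 66%, against 87% at 0.05.
- SD 4 (σ = 4): Φ(1.554 − 2.690) = Φ(−1.136) = 13%, against 34% at 0.05.

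For 80% power at the 0.00714 level, n would be 43 or 171 per group before dropout.

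**The case against.** The strongest reply is that Sample size {14} settles the matter. MDA is named as the primary variable, the trial is sized on it, and on that reading the primary error rate is 5% with everything else supportive. This stands as a conditional statement, and the inflation above applies only if Outcomes {12} governs. But nothing gives one section precedence over the other. Likewise, a rule that all seven must succeed would remove the inflation, but none is stated.

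Three stronger readings are tempting and should not be drawn.

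- **That the protocol declares seven primary variables.** It declares two domains. Seven is a count assembled from other sections, and the abstract introduces the biomarkers as examples.
- **That a significant change within the selenium arm would count as success.** The abstract, {20a} and {20b} all assign the selenium effect to ANCOVA, a between-group analysis. The paired test is said only to examine change within groups. Reporting it as efficacy would be misuse of the plan, not the plan itself. Any figure for how often one arm alone would reach significance needs a common change that the document does not give, and with independent arms and equal change it cannot exceed p(1 − p) = 25%. Regression to the mean is also a narrower worry than it may seem, because the entry rule selects on attack frequency and not directly on the biomarkers or severity.
- **That three competing tests are prescribed for each outcome.** The t-test is described thus: "Independent sample t-test will be used to detect differences in quantitative variables between intervention and control groups". Since {20b} selects covariates by between-group differences, it may serve for baseline comparison. The text is ambiguous.

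**Conclusion.** The contradiction is real and nothing in the article resolves it. Under the Outcomes {12} reading, with any one variable sufficing, the chance of a false-positive primary result is 30% for independent tests and about 11% to 27% at assumed common correlations of 0.9 to 0.3, against the 5% in Sample size {14}. Under the MDA-only reading it is 5%. The size therefore rests on three assumptions: which section governs, the count of seven, and the correlation. That the two sections conflict rests on none of them. The matter must be fixed, because it determines what the trial may conclude.

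**What to change.** Reconcile Outcomes {12} and Sample size {14} by a dated amendment made before the codes are unlocked. The protocol version is dated 17 February 2024 and the last visit was expected on 29 February 2024, so timing matters. Under section {25} the change also needs Ethics Committee approval and a registry update.

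- **Simplest option:** keep MDA, the variable used for sizing, as the single primary outcome. Compare the arms at end of treatment by ANCOVA adjusted for baseline MDA, at two-sided 0.05. This model is a recommendation; the sample-size formula itself is an unadjusted comparison of two means. Make NO, TAC, TOS, severity, frequency and duration secondary, either reported with confidence intervals or tested by Holm.
- **If the sponsor keeps all seven as primary:** apply Holm across them and restate the power, which at the first step and 33 per group is about 66% or 13% for MDA, depending on whether 4.00 is the variance or the SD.
- **Either way:** state that the between-group ANCOVA decides efficacy and that paired within-group tests are descriptive only.

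The cost of the first option is an amendment and fewer outcomes that can be claimed as confirmatory. The Holm option also costs power.

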### Participant timeline {13}

The study flow chart and timeline are presented in Figs. 1 and  2, respectively. The study protocol was designed and developed in accordance to the Standard Protocol Items: Recommendations for Interventional Trials (SPIRIT).

**Fig. 1 Fig1:**
[figure not shown]
The protocol flowchart and timeline of the study

**Fig. 2 Fig2:**
[figure not shown]
Schedule of enrolment, intervention, and assessment based on SPIRIT guidelines. The “X” refers to what is done in the given period. Abbreviations: WK, week

### Sample size {14}

The sample size was calculated based on means and standard deviations for the primary variable, which is MDA levels, reported in the study of Razavi et al. [19], considering a type I error of 5% (α = 0.05) and type II error of 20% (β = 0.20, power = 80%). Sample size was calculated using the following formula [20]:$$n=\frac{2{(\mathrm{a }+\mathrm{ b})}^{2} {\upsigma }^{2}}{{(\upmu 1 -\upmu 2)}^{2} }=33$$

*n* = the sample size in each group.

μ1 = the mean for malondialdehyde in the intervention group: -0.13 μmol/L based on the study of Razavi et al. [19]).

μ2 = the mean for malondialdehyde in the control group: 1.4 μmol/L based on the study of Razavi et al. [19]).

σ = the variance (SD) for mean concentrations of malondialdehyde: 4.00 (the average SDs reported for malondialdehyde in the control and intervention groups of Razavi et al.’s study [19]).

a = the conventional multiplier for alpha = 0.05 that was 1.96.

b = the conventional multiplier for power = 0.80 that was 0.842.

Based on the formula, we will need a sample size of 33 for each group. Considering a drop-out rate of 10%, we plan to recruit 36 migraine patients in each group.

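### The 33 per group for 80% power cannot be reproduced from the printed formula and inputs: they give 108 if 4.00 is a standard deviation and 27 if it is a variance

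*Protocol article*

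**What the plan says.** All of this stands in the protocol article, Sample size {14}. MDA is named as the primary variable for the calculation, and the inputs are taken from one cited study. The section sets the error rates ("considering a type I error of 5% (α = 0.05) and type II error of 20% (β = 0.20, power = 80"%) and uses the usual per-group formula for two means, n = 2(a + b)²σ²/(μ1 − μ2)². The inputs are:

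- μ1: "the mean for malondialdehyde in the intervention group: -0.13" µmol/L
- μ2: "the mean for malondialdehyde in the control group: 1.4" µmol/L
- σ: "the variance (SD) for mean concentrations of malondialdehyde: 4.00", explained as an average of the SDs reported for the two groups of the cited study
- a: "the conventional multiplier for alpha = 0.05 that was 1.96"
- b: "the conventional multiplier for power = 0.80 that was 0.842"

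The result is "Based on the formula, we will need a sample size of 33 for each group". The last step is "Considering a drop-out rate of 10%, we plan to recruit 36 migraine patients in each group".

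**The concern.** The formula, all its inputs and its result are printed, so the calculation can be checked directly, and it does not close. Two further features of the inputs make it unclear which figure is at fault. First, 4.00 is called a variance and an SD in the same line. Secondly, one of the means is negative, which is impossible for a concentration, while σ is described as belonging to concentrations.

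This is the only power statement in the protocol. If the SD really is 4.00, a reader who meets a null MDA result would take it to come from a trial with an 80% chance of detecting the planned difference, when that chance was about one in three. If 4.00 is a variance, the trial is somewhat better powered than claimed. As printed, the section does not let a reader tell which.

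**Working it through.** **Inputs (all from Sample size {14}).** a = 1.96 (two-sided 5%), b = 0.842, so a + b = 2.802 and 2(a + b)² = 15.702. The difference is |−0.13 − 1.4| = 1.53, and 1.53² = 2.3409.

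**Trying to reproduce 33.**

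- 4.00 as SD, so σ² = 16: n = 15.702 × 16 / 2.3409 = 107.3, so 108 per group.
- 4.00 as variance, so σ² = 4: n = 15.702 × 4 / 2.3409 = 26.8, so 27 per group.

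Neither is 33. With the difference kept at 1.53, one-sided alpha, 90% power, or a leading factor of 1 or 4 do not give 33 either. Dropping the minus sign on −0.13 (difference 1.27) gives 155.8 with SD 4 and 38.9 with variance 4.

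**Inputs that would give 33.** They differ from those printed. Two examples:

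- Difference 1.53 with an SD of about 2.2: 15.702 × 2.2² / 2.3409 = 32.5, rounded up to 33. Solving for exactly 33 gives SD 2.22.
- Variance 4 with a difference of 1.4, ignoring μ1: 15.702 × 4 / 1.96 = 32.05, rounded up to 33.

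Either could be the origin of the figure; the document does not show which.

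**Power for a difference of 1.53 (two-sided 5% t-test, noncentral t).**

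| Reading of 4.00 | n by formula | Power at 33 per group | Power at 36 per group |
|---|---|---|---|
| SD 4 | 108 | 33% | 36% |
| Variance 4 (SD 2) | 27 | 86% | 89% |

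**Difference detectable with 80% power if the SD is 4.** It is 2.85 µmol/L at 32 per group, 2.80 at 33 and 2.68 at 36. The figure at 33 is 2.80/1.53 = 1.8 times the planned difference.

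**Drop-out step.** 33/0.9 = 36.7, so 37 per group. Recruiting 36 leaves 36 × 0.9 = 32.4, about 32 completers. At 32 per group with SD 4, power for 1.53 is about 33% (0.325).

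**The case against.** The strongest reply is that the direction of the error is not established. A reader might infer that the trial's real power is 33–36%. That holds only if 4.00 is an SD. The SD reading has the better support: the symbol is σ, the formula squares it, the section says it works from means and SDs, and 4.00 is explained as an average of SDs. But the label also says variance, and on that reading 33 per group exceeds the 27 needed and the 80% claim is conservative. The cited study is not at hand, so neither 33% nor 86% can be called the true power. This objection stands and limits the conclusion to non-reproducibility, with the size conditional on the reading.

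A reader might also infer that 33 can only have come from variance 4 with a difference of 1.4. That is not supported, since a misprinted SD of about 2.2 explains it equally well. Likewise, the means are presumably changes from baseline, but a sign or transcription error in −0.13 cannot be excluded without the source.

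It may be said that the planned ANCOVA recovers the lost power. The formula has no correlation term, and the protocol states no correlation or baseline adjustment for this calculation. If 4.00 is the SD of concentrations, a baseline-adjusted analysis would need 1 − ρ² = 33/107.3, so ρ of about 0.83, for 33 per group to suffice. If 4.00 is the SD of changes (equal variances assumed), the factor is (1 + ρ)/2, and no positive correlation would do.

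Finally, the drop-out shortfall is about one participant per group, and 33 × 1.1 = 36.3 is a common shortcut, so this is minor. Trial status dates this version 17 February 2024 and expects the last visit on 29 February 2024, so enrolment cannot sensibly change. That limits the remedy to wording but leaves the misstatement in place.

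**Conclusion.** The point holds. The stated 33 per group for 80% power does not follow from the printed formula and inputs on either reading of 4.00: the formula requires 108 (about 3.3 times the stated figure) if it is an SD, or 27 if it is a variance. On the better-supported SD reading, power for 1.53 µmol/L is about 33% at 33 per group and 36% at 36; on the variance reading it is about 86% and 89%. These figures assume the printed difference of 1.53, 1:1 allocation and an unadjusted two-sided t-test at 5%. The uncertainty over whether means and SD are on the same scale is a separate defect, because a difference in changes set against an SD of concentrations would not be a valid calculation for either analysis. The arithmetic mismatch is certain; the trial's actual power is not determinable from the document.

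**What to change.** In Sample size {14}:

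1. Recheck the cited study and state whether 4.00 is an SD or a variance.
2. State whether μ1, μ2 and σ refer to changes from baseline or to concentrations, and put all three on one scale.
3. Correct whichever is wrong, the input or the result, so that the formula reproduces the stated n.
4. Restate the power or the detectable difference for 36 randomised per group, about 32 completers. If SD 4.00 is confirmed, that is about 33% power for 1.53, or 80% power for about 2.85 µmol/L, and the claim of 80% power should be removed. If 4.00 is a variance, report 27 as the formula's result and the higher power that follows.
5. Minor: note that 10% drop-out from 36 leaves about 32, just below 33.

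The cost is a source check and a rewritten paragraph. Under the SD reading the stated power becomes less favourable. Conduct, analysis and enrolment are unaffected, and no additional participants are called for.

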### Recruitment {15}

Participants will be recruited from individuals who were referred to the neurology clinic of Al-Zahra Hospital, affiliated with Isfahan University of Medical Sciences, Isfahan, Iran. An expert neurologist will evaluate the diagnosis of migraine according to ICHD-3 criteria, and those with a definite migraine diagnosis will be then screened according to the inclusion/exclusion criteria by the principal investigator (AB). All eligible participants will be asked to provide written informed consent.

## Assignment of interventions: Allocation

### Sequence generation {16a}

After recruitment, stratified block randomization will be performed based on participants’ age (18 to 39 and 40 to 65 years) and sex (male or female) across the two groups. Then, within each of the aforementioned strata, eligible participants will be randomly assigned in a 1:1 ratio to receive either selenium or placebo. Balanced randomization will be generated using an online tool (https://www.sealedenvelope.com/simple) by a person who is not involved in the study. Participants in the intervention group (*n* = 36) will receive a tablet containing 200 µg selenomethionine daily, while the placebo group (*n* = 36) will receive a tablet containing 200 µg starch daily.

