### Eligibility criteria {10}

#### Inclusion criteria

Participants who (1) have a confirmed migraine diagnosis according to the International Classification for Headache Disorders (ICHD-3) criteria [18] by an expert neurologist, (2) are aged between 18 and 65 years, and (3) experience at least two migraine attacks per month, will be included. No restrictions on the type of migraine will be considered; thus, patients with all types of migraine headaches, including migraine with/without aura and episodic/chronic migraine headaches, will be included.

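### Baseline headache burden is fixed neither in allocation nor as a covariate: ANCOVA adjusts only for variables that differ significantly between arms, so moderate chance imbalance on the headache outcomes goes uncorrected

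*Protocol article*

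**What the plan says.** Inclusion criteria: participants must "experience at least two migraine attacks per month". No upper limit is set, and "patients with all types of migraine headaches, including migraine with/without aura and episodic/chronic migraine headaches, will be included".

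Outcomes {12}: the primary outcome is to "investigate the effect of selenium on oxidative stress and clinical symptoms in migraine patients". Under Migraine symptoms assessment, frequency and duration are "evaluated as the number of attacks per month and the mean duration of attack in each day, respectively", so frequency is measured in the same unit as the eligibility floor. The abstract states that severity, frequency and duration are all measured at baseline and at the end of the study.

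Sequence generation {16a}: "stratified block randomization will be performed based on participants’ age (18 to 39 and 40 to 65 years) and sex (male or female". This gives four strata, within which "eligible participants will be randomly assigned in a 1:1 ratio to receive either selenium or placebo". Sample size {14}: "we plan to recruit 36 migraine patients in each group".

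Analysis: Statistical methods {20a} lists independent t-tests between groups and names ANCOVA as the method for detecting the effect of selenium. It says that potential confounders will be considered, without naming any. The section on additional analyses {20b} supplies the only selection rule: covariates are those on which the two arms turn out to differ significantly. It plans no subgroup analyses.

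**The concern.** Eligibility deliberately widens the population along an axis that is itself an outcome. Baseline attack frequency is the pre-treatment value of a headache outcome, and one would expect it to predict the week-12 value. Allocation balances two other variables, so any balance on headache burden is left to chance in 72 patients.

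That would matter little if the analysis always adjusted for baseline headache burden. The stated rule does so only after a significant baseline difference. This is a poor trigger: how far a covariate distorts an estimate depends on its link with the outcome as well as on the size of the imbalance, and a significance test in a small trial misses moderate imbalance. The rule also tends to leave out age and sex, since stratification is meant to prevent them from differing. At stake are the precision of the symptom comparisons and how readily a positive or null symptom result can be explained by unequal arms at entry.

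**Working it through.** The plan gives no figure on this point to reproduce. Inputs from the document: 36 per arm, 1:1 allocation, two-sided 5% significance. The share of chronic patients, the contrast in frequency between types and the correlation between baseline and week 12 are not given; they are assumed below and shown as ranges.

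**1. Baseline frequency as a continuous variable**
- SD of the standardised between-arm baseline difference: sqrt(2/36) = 0.236.
- P(gap > 0.25 SD): 0.25/0.236 = 1.06, two-sided probability 0.289. P(gap > 0.50 SD) = 0.034.
- Smallest gap that a baseline t-test calls significant: 1.994 × 0.236 = 0.47 SD (70 degrees of freedom), reached in about 5% of randomisations.
- Gap above 0.25 SD but below the trigger: about 0.289 − 0.046 = 0.243, roughly a quarter of randomisations.
- Resulting shift in an unadjusted comparison is correlation × gap. At an assumed correlation of 0.5 it is 0.125 to 0.235 outcome SDs.

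**2. Migraine type as a binary variable**

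The between-arm gap in the number of chronic patients, with two independent Binomial(36, p) counts and, as a check, with the total among 72 held fixed (hypergeometric):

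| Assumed chronic share | P(gap ≥ 5), binomial | P(gap ≥ 5), total fixed |
|---|---|---|
| 15% | 13.5% | 19% (11 of 72) |
| 30% | 24.6% | 20% (22 of 72) |
| 50% | 28.9% | 24% (36 of 72) |

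The columns differ partly because an even fixed total allows only even gaps, so that 5 or more then means 6 or more.

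When the significance rule would act, near a 30% share (uncorrected chi-square, 36 per arm):
- 14 v 8: chi-square 2.36, p = 0.12, not adjusted
- 15 v 8: chi-square 3.13, p = 0.08, not adjusted
- 15 v 7: chi-square 4.19, p = 0.04, adjusted

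If chronic patients had 6 to 10 more attacks a month (assumed), the 14 v 8 split would move the difference in mean frequency by 6/36 × 6 = 1.0 to 6/36 × 10 = 1.7 a month with no treatment effect.

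**3. Type I error and precision**

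Simulation under no effect (20,000 runs per setting, 36 per arm):

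| Baseline–outcome correlation | Unadjusted | ANCOVA always | ANCOVA only after significant baseline test |
|---|---|---|---|
| 0.3 | 4.8% | 5.1% | 4.6% |
| 0.5 | 5.0% | 5.3% | 4.5% |
| 0.7 | 5.1% | 5.0% | 3.7% |
| 0.8 | 4.9% | 4.9% | 3.0% |

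The significance-driven rule does not inflate type I error; it becomes conservative as the correlation rises. Fixed adjustment reduces residual variance by about the squared correlation: 9% at 0.3, 25% at 0.5, 49% at 0.7 and 64% at 0.8.

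**The case against.** The strongest reply is that stratifying on age and sex is a legitimate choice that contradicts nothing else in the article. Chance imbalance is ordinary sampling variation, already contained in the standard error. That stands: averaged over randomisations the comparison is unbiased, and the simulation supports it.

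A second reply is that the article names ANCOVA as its main method, that ANCOVA often implies the baseline value as covariate, and that covariate lists usually belong in an analysis plan, which is not shown. This stands in part: an unnamed covariate list would be no finding. But the article does not leave the choice open; it states a selection rule, and that rule is what fails here.

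Third, the trial was sized on malondialdehyde, and nothing in the document links headache burden to that marker. This stands and limits the point to the headache outcomes.

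A reader might infer more: that migraine type is the factor that most separates patients, that the strata are wrong, and that migraine type should take the place of age. The document gives no chronic share, no contrast and no correlation, so it supports no ranking of factors. Swapping a stratum is a trade-off, and it is also too late. The last visit is anticipated on 29 February 2024, and subtracting 12 weeks (84 days) puts the last randomisation at about 7 December 2023, before this protocol version of 17 February 2024. Rewriting the allocation section would misdescribe what was done.

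**Conclusion.** The point holds as a weakness of precision and interpretability in the analysis of headache severity, frequency and duration. Neither allocation nor the stated covariate rule secures adjustment for baseline headache burden. In about 24% of randomisations a baseline gap above 0.25 SD would fall short of the significance trigger and stay unadjusted. That figure rests only on 36 per arm and an approximately normal mean difference. The shift of 1.0 to 1.7 attacks a month and the chronic-share probabilities rest on assumptions and serve as illustration; no such contrast is assumed for severity or duration.

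It would be wrong to conclude that the symptom results are biased or that false positives are inflated: unadjusted and always-adjusted tests hold about 5%, and the stated rule gives 3.0% to 4.6%. The trial's validity is not in question.

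**What to change.** Leave Sequence generation {16a} as it stands. Before the codes are unlocked, amend Statistical methods {20a} and the additional-analyses section {20b} to say that the between-arm ANCOVA for severity, frequency and duration always includes:

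- the baseline value of that outcome;
- the stratification factors, age group and sex;
- migraine type (episodic v chronic), where it was recorded at screening.

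These terms enter regardless of any observed imbalance and replace selection by baseline significance tests. The baseline value is the main term, because the trial already measures it. Migraine type is conditional: the article has a neurologist confirm the diagnosis but does not list episodic or chronic status among the recorded baseline variables.

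The cost is a handful of model terms in 72 patients, with no extra patients, visits or measurements. Because the codes are unlocked only after trial completion, the change can be made blind. Under Plans for communicating important protocol amendments {25}, a change of methods needs ethics committee approval and an entry in the registry.
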